### Sample Size

Based on our pilot study, Cohen's *d* = 0.684, effect size =0.324. Cohen's d and the effect sizes were calculated for between-group differences of means of the level compliance of participation in cognitive dysfunction management using an independent-groups pre-test and post-test design (IGPP). Sample size estimation was conducted using statistical software G^*^power. The analysis, with an independent *t*-test using β = 0.95 and α = 0.05, requires a total sample size of 114 participants. Considering a 15% dropout rate, our total sample size comes to 132 participants (66 cases for both the intervention and control groups).

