#### Data Collection

Before randomized allocation, the baseline data (T0) will be collected at a community health care center by the staff blinded to group allocation, including socio-demographic profile, primary outcomes and secondary outcomes; primary outcomes, and secondary outcomes will be measured again at the end of the intervention (T1) and 3 months after intervention (T2). Table 2 shows the assessment and timeline of the study.

**Table 2 T2:** Summary of study assessments and time-lines.

	**Questionnaire items**	**Time point**				
		**Baseline**	**Randomized allocation**	**Intervention**	**Post intervention**	**Follow-up 3 months**
		**T0**			**T1**	**T2**
Enrollment						
Eligibility screening						
Informed consent						
Screening	**General information**					
	Demographic information	✓				

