### Statistical Analysis

Data collection will be conducted in a single room and kept in a password protected computer folder. Collected data will be encoded in Excel and double-checked. Data processing and statistical analysis will be conducted using SPSS 22.0. Descriptive statistics will summarize demographic data and observable variables using frequencies and percentages for categorical variables, means ± standard deviations for continuous variables. We will employ exploratory analysis (normality testing and distribution curves) to examine the distribution of data. The proportionality of baseline data for both groups will be compared using the non-parametric Wilcoxon test, the Chi–square test, and the *T*-test. A 2 (group) × 3 (time) ANOVA will be used to determine the effect of the group factors, the intervention group and control group differences within-group over time, and interaction effects. Simple effect analysis will be added when there is an interaction between group factors and time factors. The intention-to-treat principle will follow data analysis. A two-tail *P*-value of < 0.05 will be considered statistically significant.

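### The 2 × 3 ANOVA counts the pre-randomisation baseline as a time level, so its group effect is not the treatment effect, and the 95% power belongs to a t-test that the outcome analysis does not use

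*Protocol article*

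**What the plan says.** **Analysis.** The Statistical Analysis section states: "A 2 (group) × 3 (time) ANOVA will be used to determine the effect of the group factors", together with change over time and the interaction. It continues: "Simple effect analysis will be added when there is an interaction between group factors and time factors". The t-test appears there only among the methods for comparing the arms at baseline. The significance level is two-sided 0.05.

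**Timing.** Data Collection states: "Before randomized allocation, the baseline data (T0) will be collected at a community health care center by the staff blinded to group allocation". The outcomes are measured again at the end of the intervention (T1) and three months later (T2). Neither visit is named as primary.

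**Sizing.** The Sample Size section reports Cohen's d as "0.684, effect size =0.324", for the between-group difference in the compliance score, obtained "using an independent-groups pre-test and post-test design (IGPP"). The calculation is for an independent t-test "using β = 0.95 and α = 0.05, requires a total sample size of 114 participants". Inflation for 15% dropout gives 132, or 66 per arm.

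**The concern.** At T0 the arms can differ only by chance. A group main effect that averages T0, T1 and T2 therefore mixes one level with no effect into the two that can carry one. It estimates something smaller than the treatment effect at either visit if the benefit is equal at both.

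The other route to a treatment comparison is the interaction, a 2-df test. The between-group contrast at a given visit is examined only if that test is significant.

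The sample size was computed for neither of these tests, so the stated power cannot be carried over to the analysis described. A real benefit could be missed because the diluted main effect is read as the answer, or because the interaction condition is not met.

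**Working it through.** **Inputs from the protocol.** d = 0.684, two-sided α = 0.05, total 114 (57 per arm), 1:1 allocation, T0 before randomisation.

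**Assumptions (not in the protocol).** Within-person correlation ρ of 0.3 to 0.7, the same between all visits; equal SDs; d = 0.684 at T1 on the raw-score SD; a T2 effect that is kept (0.684), halved (0.342) or lost (0).

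**1. The plan's own figure.** A two-sample t-test (noncentral t) with d = 0.684 and power 0.95 needs 56.53 per arm, so 57 per arm and 114 in total, with power 0.952. The stated N reproduces if the value printed as β is read as power. The second figure, 0.324, is the same effect as a correlation: 0.684/√(0.684² + 4) = 0.324.

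**2. Group main effect.** The raw difference is (0 + d1 + d2)/3, and the SD of a person's three-visit mean is √((1 + 2ρ)/3).

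- Kept: raw difference (0 + 0.684 + 0.684)/3 = 0.456, one third below 0.684.
- Standardised at ρ = 0.3, 0.5, 0.7: 0.456/0.730 = 0.624, 0.456/0.816 = 0.558, 0.456/0.894 = 0.510. These are about 9%, 18% and 25% below 0.684.

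**3. Interaction.** Noncentral F with 2 and 2 × (114 − 2) = 224 df, and noncentrality (57/2) × SS/(1 − ρ), where SS is the sum of squared deviations of (0, d1, d2) from their mean.

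- Kept or lost: SS = 0.312, noncentrality 12.7, 17.8, 29.6 at ρ = 0.3, 0.5, 0.7.
- Halved: SS = 2 × 0.342² = 0.234, noncentrality 9.5, 13.3, 22.2.

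**4. T1 contrast after the interaction condition.** Simulated, 8,000 runs per cell, requiring both the interaction and the T1 contrast to be significant.

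**5. Baseline-adjusted T1 contrast.** Effective d = 0.684/√(1 − ρ²) = 0.717, 0.790, 0.958.

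Power at 57 per arm, for ρ = 0.3 / 0.5 / 0.7:

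| Test | T2 effect kept | halved | lost |
|---|---|---|---|
| Group main effect, T0–T2 | 0.91 / 0.84 / 0.77 | 0.70 / 0.60 / 0.53 | 0.38 / 0.32 / 0.27 |
| Interaction (2 df) | 0.90 / 0.97 / 0.999 | 0.79 / 0.91 / 0.99 | 0.90 / 0.97 / 0.999 |
| T1 contrast after interaction | 0.86 / 0.93 / 0.95 | 0.77 / 0.87 / 0.95 | 0.87 / 0.94 / 0.95 |
| Unadjusted T1 t-test | 0.952 | 0.952 | 0.952 |
| Baseline-adjusted T1 contrast | 0.967 / 0.987 / 0.999 | same | same |

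At ρ = 0.6 the interaction has power 0.991, 0.961 and 0.991 (kept, halved, lost).

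For 95% power on the group main effect the total N is 136, 170 and 202 at ρ = 0.3, 0.5 and 0.7, even if the effect is fully kept. With all 66 per arm analysed, its power in that case is 0.945, 0.890 and 0.828.

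**The case against.** - **The interaction is a legitimate test and often strong enough.** In a randomised trial the group × time interaction tests differential change, and the simple-effects rule suggests that it is meant to be the operative test. At ρ = 0.6 and above its power is 0.96 or more in all three T2 scenarios. This stands. A reader might infer that the trial is underpowered whichever test is used; the documents do not support that.
- **The condition often costs little.** At ρ = 0.7 the conditional T1 contrast keeps power of about 0.95. The largest loss shown, to 0.77, needs both ρ = 0.3 and a halved T2 effect. This stands too, but in none of these scenarios does the condition improve on the plain t-test.
- **Scale of d.** The Sample Size section does not say which SD was used. If d was scaled to the SD of change, the raw-scale d is 0.684 × √(2(1 − ρ)). The factor (1 − ρ) then cancels, and the interaction has power 0.97, 0.91 and 0.97 (kept, halved, lost) at any ρ. The main effect, if the benefit is kept, has standardised size 0.739, 0.558 and 0.395 and power 0.97, 0.84 and 0.55 at ρ = 0.3, 0.5 and 0.7. So on this reading it passes 0.95 in one case.
- **One third is a raw-scale figure.** Averaging also reduces variance, so it is not the standardised loss when the effect persists.
- **T1 is inferred.** No section names it as primary. The pre-test/post-test effect size only makes it likely.
- **Timing and direction.** The simple effects supply both once the condition is met.
- **An analysis plan may say more.** True of the choice of covariates, so the absence of baseline adjustment is not itself a fault here. But the article does state the ANOVA, the condition and the sizing test, and these do not match.

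**Conclusion.** The point holds in a limited form. The group main effect over T0, T1 and T2 is not the treatment effect, because one of its three levels precedes randomisation. On the raw-score reading of d its power is below the stated 0.95 in every scenario tabulated, from 0.91 down to 0.27. The 95% is a property of an independent t-test that the outcome analysis does not use. The interaction may have less power than that (0.79 to 0.90 at ρ = 0.3; 0.91 at ρ = 0.5 if the T2 effect halves) or more.

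The size of any shortfall depends on ρ, the T2 effect and the scale of d, none of which the protocol gives. The mismatch between the sizing test and the analysis does not depend on them. No bias in the trial's conduct or data is implied. This should be fixed, but it is not a fatal fault in the design.

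**What to change.** 1. State that the group main effect over T0–T2 will not be interpreted as the treatment effect.
2. Remove the rule that makes the between-group contrast conditional on a significant interaction.
3. Make the primary analysis the baseline-adjusted between-group difference in compliance score with its 95% CI. Use ANCOVA, or a mixed model for T1 and T2 with T0 as covariate and terms for group, visit and group × visit.
4. Name one primary time point. The sponsor must confirm it; T1 is the likely one. Report the other visit as secondary.
5. State which SD d refers to, and give the power for the chosen contrast. With 57 per arm it is at least about 0.95 if d = 0.684 is the difference at that visit on the raw-score SD.
6. Keep the 2 × 3 ANOVA as a supportive analysis if wanted.

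**Cost.** Wording in two sections. T0 is already collected for every outcome, and the named software (SPSS) fits both models. No extra participants, visits or data are needed. The article describes the trial as ongoing, so the change should be made and dated before any unblinded analysis.

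### The 2 × 3 ANOVA named for the outcomes does not by itself deliver the promised intention-to-treat analysis, because on its usual reading it drops everyone who misses T1 or T2

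*Protocol article*

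**What the plan says.** The Statistical Analysis section names one method for the outcomes: "A 2 (group) × 3 (time) ANOVA will be used to determine the effect of the group factors", together with within-group change over time and the interaction, followed by simple-effect analysis if there is an interaction. The Abstract names the same ANOVA. On software it says: "Data processing and statistical analysis will be conducted using SPSS 22.0". The same paragraph then adds: "The intention-to-treat principle will follow data analysis". It names no SPSS procedure, no imputation and no complete-case rule.

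Under Data Collection and in Table 2, the primary and secondary outcomes are measured in the same people at baseline (T0), at the end of the 8-week intervention (T1) and 3 months later (T2).

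The Sample Size section anticipates attrition: "Considering a 15% dropout rate, our total sample size comes to 132 participants".

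Two other places affect who is analysed. Study Design and Participants withdraws from the study people with certain events during the trial or follow-up. Table 1 lists serious events during the intervention, and loss to follow-up, among the exclusion criteria.

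**The concern.** Time is a within-person factor with three levels, and the section uses the vocabulary of classical repeated-measures ANOVA. That model works on a complete set of three scores per person. The standard repeated-measures GLM routine in SPSS removes the whole case if any score is missing. A participant seen at T0 and T1 but not at T2 therefore contributes nothing to the group × time tests, not even the T1 comparison. The other literal reading, a two-way ANOVA that treats the visits as independent observations, would keep those rows but ignore the correlation within a person. Neither reading keeps all randomised participants in a sound analysis without a further step.

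The larger stake is bias. Analysing completers is safe if dropout is unrelated to outcome. Here the arms differ in ways that could affect who stays:

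- The intervention arm attends weekly for 45–60 minutes. The control arm attends every two weeks for 45 minutes at another centre.
- Study Design and Participants ties a gift to each completed session of the intervention programme and mentions none for control sessions. The interview gifts under Retention Strategies are not limited to one arm.
- The first primary outcome is a compliance scale that covers self-efficacy and perceived barriers, so people who leave may well score differently from those who stay.

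None of this shows that dropout will be informative, but it makes dropout unrelated to outcome a poor default assumption.

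**Working it through.** **Inputs from the Sample Size section.** d = 0.684 (given as "0.684, effect size =0.324"); α = 0.05, two-sided according to Statistical Analysis; power 0.95 (printed as β); 114 evaluable; 15% dropout; 132 in total, 66 per arm.

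**The plan's own figures.**
- Two-sided independent t-test, noncentral t: d = 0.684, α = 0.05 and power 0.95 give 56.53 per arm, so 57 per arm and 114 in total. This matches.
- 0.324 is the same effect expressed as r: 0.684 / √(0.684² + 4) = 0.324.
- Dropout allowance: 114 × 1.15 = 131.1, or 132 rounded up. This matches the stated total. Dividing instead gives 114 / 0.85 = 134.1, or 135.

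**People dropped by listwise deletion.** This takes the 15% as the share missing at least one follow-up visit.
- Dropped: 0.15 × 132 = 19.8, about 20.
- Kept: 0.85 × 132 = 112.2, about 112, or 56 per arm.

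**Power**, with the plan's own t-test as a stand-in for the ANOVA (noncentrality d × √(n/2), df = 2n − 2):

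| n per arm | Noncentrality | Power |
|---|---|---|
| 66 (everyone observed) | 0.684 × √33 = 3.93 | 97.4% |
| 57 (target) | 0.684 × √28.5 = 3.65 | 95.2% |
| 56 (complete cases) | 0.684 × √28 = 3.62 | 94.8% |

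If instead 15% were lost at each of T1 and T2 (an assumption), 132 × 0.85² = 95.4 would remain, with power of about 91%.

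**Observed T1 scores discarded.** The protocol does not split dropout between T1 and T2, so this is shown as a range. The last column compares simple sample sizes.

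| Share of dropouts who miss only T2 (assumed) | T1 scores observed | T1 scores analysed | Discarded | T1 interval wider by |
|---|---|---|---|---|
| none | 112.2 | 112.2 | 0 | 0% |
| half | 122.1 | 112.2 | 9.9 | √(122/112) = 1.044, about 4% |
| all | 132 | 112.2 | 19.8 | √(132/112.2) = 1.085, about 8% |

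**Bias, on assumed values.** If a share p of an arm drops out and dropouts lie δ SD below completers, the completers' mean exceeds the full-arm mean by p × δ. With the same δ in both arms, the between-arm bias is (p₁ − p₂) × δ. Taking p = 20% and 10%, which averages to the planned 15%:
- δ = 0.5: 0.10 × 0.5 = 0.05 SD, and 0.05 / 0.684 = 7% of the planned effect.
- δ = 1.0: 0.10 × 1.0 = 0.10 SD, and 0.10 / 0.684 = 15% of the planned effect.

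**The case against.** A reader might infer that the plan prescribes a complete-case analysis and so contradicts its own intention-to-treat sentence. The document does not support that. It does not use the term repeated measures for the ANOVA and states no rule for deleting incomplete cases. Naming SPSS 22.0 does not settle the procedure either, because that package also contains a mixed-model routine. An ANOVA on imputed data, with everyone in the allocated arm, would satisfy both statements. Missing-data handling is also commonly left to a fuller protocol or analysis plan, so its absence from the article is not a fault. This part of the objection stands.

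It would likewise be too strong to say that these people are lost from every test: the baseline comparisons need only T0. The planned enlargement from 114 to 132 absorbs nearly all of the power loss. The precision and bias figures depend on a dropout pattern that the protocol does not give. Unequal dropout alone does not bias the comparison; dropouts must also differ in outcome.

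What the objection does not remove is that the article chose a method, and on its ordinary reading that method needs an additional step to honour the intention-to-treat promise. The surrounding text offers no such step. It sizes the trial on evaluable participants and lists loss to follow-up as an exclusion criterion. Correcting Table 1 alone would not help, because the classical ANOVA would still drop incomplete cases.

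**Conclusion.** The point holds in a limited form: the stated ANOVA does not by itself deliver the stated intention-to-treat analysis. This rests on the classical repeated-measures reading, which is the likely one but is not spelled out. On that reading, and at the plan's own 15% dropout, about 20 of 132 randomised participants leave the group × time tests, together with any T1 scores from those who miss only T2. The loss of power, under three percentage points, is not the reason to act. The reason is possible bias where dropout is related to outcome and differs by arm; the 0.05 to 0.10 SD illustrates its scale and is not a forecast. The conflict stated most directly in the document's own words is between the intention-to-treat sentence and the withdrawal and exclusion wording in Study Design and Participants and in Table 1.

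**What to change.** In Statistical Analysis, specify the group × time analysis as a likelihood-based linear mixed model (the MIXED procedure in SPSS, unstructured covariance over the three visits) with all randomised participants in their allocated arm and all observed visits. Multiple imputation before the ANOVA would be an acceptable alternative if it is stated.

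Reconcile the intention-to-treat sentence with Study Design and Participants and with Table 1, so that the text says plainly whether people withdrawn or lost after randomisation stay in the analysis set.

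The mixed model assumes that data are missing at random. It does not remove bias from dropout that depends on unobserved outcomes, and for someone lost before T1 it has only the baseline score. A delta-adjusted sensitivity analysis would address that and is optional.

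The cost is a few sentences of text and a little analysis time, with no new data and no new software. It is best settled before anyone sees outcome data by arm.

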### Primary Outcomes

#### Level of Compliance of Participation in Cognitive Dysfunction Management

The compliance of participation in cognitive dysfunction management will be determined using the Cognitive Dysfunction Management Compliance Scale (31). This scale was developed by our research team. It is composed of six dimensions: (1) perceived susceptibility (seven items); (2) perceived seriousness (four items); (3) perceived benefits (three items); (4) perceived barriers (seven items); (5) cues to action (three items); and (6) self-efficacy (eight items). Each item is scored based on a five-point Likert scale (1=not at all agree; 2=disagree; 3=not concerned; 4=agree; 5=very agree), (–) for reverse counting. A higher score means more adherence to cognitive management. The Cronbach's α coefficient of the overall questionnaire was 0.904, and content validity I-CVI was 0.92.

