#### Level of Knowledge of MCl

The scores of MCI knowledge will be determined using the MCI Knowledge Questionnaire. The questionnaire, designed by HY, Pan of Fudan University (32), has three domains: (1) basic knowledge of MCI (four items); (2) risk factors of MCI (eight items); and (3) prevention, treatment, and cognition of MCI (eight items). The answer for each item is true (1) or false (0). Total scores on the questionnaire range from 0 to 20, with higher scores indicating more knowledge. The Cronbach's α coefficient of the overall questionnaire was 0.85, the content validity I-CVI was 0.93 (32).

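### Two primary outcomes share one unadjusted 0.05 threshold and the trial is sized on only one of them, so the risk of a false primary claim is about 8.5–10% if either may count

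*Protocol article*

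**What the plan says.** The Primary Outcomes section of the protocol article has two entries. For compliance: "The compliance of participation in cognitive dysfunction management will be determined using the Cognitive Dysfunction Management Compliance Scale". For knowledge: "The scores of MCI knowledge will be determined using the MCI Knowledge Questionnaire". The Data Collection section and Table 2 have both measured at baseline (T0), at the end of the intervention (T1) and three months later (T2).

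The Statistical Analysis section plans a 2 (group) × 3 (time) ANOVA that yields group, time and interaction effects. Simple effects are added only where there is an interaction. The section closes with the one significance rule: "A two-tail *P*-value of < 0.05 will be considered statistically significant". The Abstract repeats the 5% cut-off. Neither place names a leading primary outcome, a primary time point or a confirmatory ANOVA effect.

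The Sample Size section rests on compliance only: "Cohen's d and the effect sizes were calculated for between-group differences of means of the level compliance of participation in cognitive dysfunction management". The input is "Based on our pilot study, Cohen's *d* = 0.684, effect size =0.324", and the result is given as "independent *t*-test using β = 0.95 and α = 0.05, requires a total sample size of 114 participants". Then: "Considering a 15% dropout rate, our total sample size comes to 132 participants".

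**The concern.** A 0.05 test on each of two primary outcomes holds the error at 5% per outcome. It holds it for the trial as a whole only if both must succeed or if they are tested in a fixed order, and the article states neither.

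A second choice is left open. Each outcome's ANOVA gives a group F test and an interaction F test, and the text does not say which one carries the claim.

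The two outcomes also answer different questions. The Background already accepts that health education raises disease knowledge, and the Discussion presents behaviour change as the open question. The intervention arm has 8 weekly sessions of 45–60 minutes (8 × 45 = 360 to 8 × 60 = 480 minutes). The control arm has one 45-minute session every two weeks over 8 weeks (4 × 45 = 180 minutes). A result on knowledge alone could therefore be presented as primary success while compliance, the outcome the trial was sized for, shows nothing.

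**Working it through.** **1. The plan's own figure.** Inputs from Sample Size: d = 0.684, alpha 0.05, and 0.95, which is printed as β but only makes sense as power. A two-sided two-sample t-test (noncentral t) needs 56.53 per arm, so 57 per arm and 2 × 57 = 114 in total. The stated 114 is reproduced. (A one-sided test would need 47 per arm.) So the full two-sided 0.05 is spent on one outcome, compliance.

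**2. Error with independent tests.** The chance of at least one false positive in k tests at 0.05 is 1 − 0.95^k.
- k = 2 (one test on each primary outcome): 1 − 0.9025 = 9.75%, or 1.95 times 5%.
- k = 4: 1 − 0.8145 = 18.5%, or 3.7 times 5%.

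**3. Error with correlated tests.** Simulation with no effect on either outcome, 57 per arm, three time points and 20,000 runs per scenario. The article gives no correlations, so these are assumed: 0, 0.5 and 0.8 between visits, crossed with 0, 0.3 and 0.6 between outcomes.

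| What counts as primary success | Range over scenarios |
|---|---|
| Between-group difference at one visit, either outcome | 8.5–10.0% |
| Interaction F test, either outcome | 8.5–10.0% |
| Group or interaction F test, either outcome | 16.6–18.9% |
| Interaction significant, then a T1 or T2 difference, either outcome | 1.4–5.9% |
| T1 and T2 tested freely, either outcome (not what is planned) | 13.3–18.5% |

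The Monte Carlo standard error near 9.75% is √(0.0975 × 0.9025 / 20,000) = 0.2 percentage points, so 10.0% is consistent with 9.75%.

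**4. Effect of a remedy on power (two-sample t-test, d = 0.684).**
- Alpha 0.05, 57 per arm: 95.2%.
- Alpha 0.025, 57 per arm: 91.5%.
- Alpha 0.025, 56 per arm (132 × 0.85 = 112 evaluable): 90.9%.
- Holding 95% at alpha 0.025 needs 65.8, so 66 per arm or 132 evaluable. With 15% dropout that is 132 / 0.85 = 155.3, or 156 randomised.

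**The case against.** The strongest defence is that the article is a condensed protocol and its statistical analysis plan is not shown. A general 0.05 threshold is compatible with a fixed sequence, where each step is at 0.05, and with a rule that both outcomes must succeed. In either case there is no inflation. The Background hypothesis and the Discussion also name compliance and knowledge together. This limits the point: one cannot say that the trial has no multiplicity rule anywhere. It does not remove it. The article fixes a threshold, designates two primary outcomes and sizes on one. The joint phrasing of the aims sets no success rule.

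A reader might infer that two outcomes at two post-baseline visits make four free tests and quadruple the error. The documents do not support that. T0, T1 and T2 enter one ANOVA per outcome, and simple effects wait for an interaction, which is a hierarchy within each outcome. Under that gate the error is 1.4–5.9%. Even four independent ungated tests give 18.5%, short of 20%.

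A reader might also take 17–19% as the error rate of the plan as written. The article never says that any significant F test means success. It leaves that route open without adopting it.

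Finally, if extra teaching time really raises knowledge, a significant knowledge result is not a false positive. That is correct: the knowledge-only scenario is a matter of what the trial may claim, separate from the error rate.

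**Conclusion.** The point holds in limited form and should be fixed. With two primary outcomes at two-sided 0.05 each and no order, split or both-must-succeed rule, the chance of a false primary claim is about 8.5–10%, roughly double the nominal level. This assumes that success on either outcome suffices and that each has one confirmatory test. It rises to about 17–19% only if the group or the interaction F test on either outcome is accepted. If both outcomes had to succeed, there would be no inflation above 5%. The ranges depend on assumed correlations, but across those examined the two-outcome figure stays between 8.5% and 10%.

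**What to change.** Add one paragraph to the analysis section, before the blinded analyst learns the allocation.

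- Name one confirmatory contrast per primary outcome, for example the between-group difference at T1. Report the other ANOVA effects and T2 as supportive.
- Preferred: test compliance first at two-sided 0.05, since the sample size is built on it, and test knowledge at 0.05 only if compliance is significant. This costs compliance no power (95.2% at 57 per arm) and needs no more participants. The price is that knowledge cannot be claimed if compliance fails.
- Alternative: keep both primary and use Holm. In the worst case compliance is tested at 0.025, and its power falls from about 95% to about 91% at 57 per arm. Restoring 95% would take 132 evaluable participants, about 156 randomised.

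The power figures are for a two-sample t-test, as in the Sample Size section, and should be rechecked for whichever contrast is named. The outcomes already labelled secondary need no relabelling for this purpose.
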